### Randomization

We will use ResMan Research Manager (RRMS) (http://www.medresman.org/login.aspx) to manage the trial data. Randomization of the trial will be completed by RRMS. According to a random sequence table generated by RRMS, participants who satisfy the inclusion criteria will be randomly allocated into one of the two groups in a ratio of 1:1. Unique identification codes and randomization numbers will be generated for each participant in RRMS.

### Allocation concealment

All researchers will receive training in allocation concealment before the study. The randomization sequence schedule will be managed and password-controlled in RRMS by an appointed research member who will not be involved in the screening or enrolling of participants. The assignments will be unknown to all researchers except for the Chinese doctor responsible for diagnoses, acupuncture, and herbal medicine formulas.

### Blinding

Because of the unique characteristics of the TCM methods used in this trial, it would be difficult to blind the researchers administering the TCM treatments and the participants. However, the researchers who are responsible for the lifestyle intervention, laboratory tests, and statistical analyses will be blind to the grouping information.

### Sample size

Given the difficulty determining an adequate sample size due to the lack of sufficient preliminary studies, we adopted a pilot study design with 40 participants per group, considering the limited research funds.

### Patient identification and enrollment

#### Source of participants

All of the participants will be identified from the Fifth Affiliated Hospital of Guangzhou Medical University. Researchers will screen and include participants mainly from outpatient clinics of the Medical Examination Centre, Department of Endocrinology and Department of Rehabilitation Medicine.

#### Diagnostic criteria (according to the ADA criteria for a diagnosis of prediabetes in 2016 [40, 41])

IFG: FPG of 5.6 mmol/L (100 mg/dL) to 6.9 mmol/L (125 mg/dL)Impaired glucose tolerance (IGT): 2-hPG after a 75-g oral glucose tolerance test (OGTT) of 7.8 mmol/L (140 mg/dL) to 11.0 mmol/L (199 mg/dL)HbA_1c_ of 5.7−6.4%

Participants who satisfy one of the above criteria will be diagnosed with prediabetes.

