#### Exclusion criteria

History of diabetes (except gestational diabetes)Cardiovascular and cerebrovascular events (cerebrovascular accident in past 6 months, history of myocardial infarction or heart failure; severe organic heart disease; aneurysm of a main artery or dissecting aneurysm; specific angina; type II degree atrioventricular block; sick sinus syndrome)Impairment of hepatic or renal function: abnormal alanine aminotransferase (ALT), aspartate aminotransferase (AST), blood urea nitrogen (BUN) or creatinine (Cr)Endocrine disease, such as hyperthyroidism, autoallergic disease, cancer or other serious or potentially fatal illnessPregnancy, preparation for pregnancy or active lactation in womenPatients with mental illness or those who are uncooperativeParticipation in other clinical trial within the last 2 weeksRefusal to provide consent for the study

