### Outcome measures

#### Endpoint events

Occurrence of type-2 diabetes (according to the 2016 ADA diagnostic criteria for prediabetes [40, 41])Blood glucose change to normal (FPG <5.6 mmol/L, OGTT 2-hPG <7.8 mmol/L, and HbA_1c_ <5.7%)

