#### Primary outcomes

Fasting plasma glucose (FPG): fasting is defined as no caloric intake for at least 8 h2-h plasma glucose (2-hPG) level after 75-g oral glucose tolerance test (OGTT): the test should be performed as described by the WHO, using a glucose load containing the equivalent of 75 g anhydrous glucose dissolved in waterGlycosylated hemoglobin (HbA_1c_)

All the primary outcomes will be tested on visit 1 (within 1 week before the study), visit 25 (after 24 weeks), and visit 26 (after 48 weeks).

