#### Additional indicators

Body Mass Index (BMI): BMI = weight (kg)/square of height (m^2^). The weight and height of participants will be measured by the same equipment in the Medical Examination Centre of the Fifth Affiliated Hospital of Guangzhou Medical UniversityIncidence of type-2 diabetes mellitus

Calculated using the following formula:$$ \mathrm{Incidence}\ \mathrm{of}\ \mathrm{diabetes}\ \mathrm{mellitus} = \mathrm{Cases}\ \mathrm{of}\ \mathrm{diabetes}\ \mathrm{mellitus}/\mathrm{Total}\ \mathrm{cases}\ \mathrm{of}\ \mathrm{each}\ \mathrm{group} \times 100\% $$
Reversion rates of FBG, 2-hPG after 75-g OGTT, and HbA_1c_ after 48 weeks of follow-up;

Calculated using the following formula:$$ \mathrm{Reversion}\ \mathrm{rate} = \mathrm{Cases}\ \mathrm{o}\mathrm{f}\ \mathrm{blood}\ \mathrm{glucose}\ \mathrm{t}\mathrm{hat}\ \mathrm{have}\ \mathrm{returned}\ \mathrm{t}\mathrm{o}\ \mathrm{normal}/\mathrm{cases}\ \mathrm{o}\mathrm{f}\ \mathrm{each}\ \mathrm{group} \times 100\% $$

BMI will be tested on visit 1 (within 1 week before the study), visit 25 (after 24 weeks), and visit 26 (after 48 weeks).

Incidence of type-2 diabetes mellitus, reversion rates of FBG, 2-hPG after 75-g OGTT, and HbA_1c_ will be calculated only on visit 26 (after 48 weeks).

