#### Bias control

Any other Western or TCM medication that the participants take during the observation period will be recorded, and drugs that have antidiabetic therapeutic effects will be prohibited. The researchers will pay close attention to the study interventions to prevent the occurrence of bias.

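### The entry rule sets no ceiling on the other two glucose indices, so a person above the prediabetes range on one index at visit 1 can be enrolled and later counted as a diabetes case

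*Protocol article*

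**What the plan says.** All references are to the protocol article.

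- **Entry.** Diagnostic criteria gives three ranges: "FPG of 5.6 mmol/L (100 mg/dL) to 6.9 mmol/L (125 mg/dL" mmol and mg units for fasting glucose, a 2-hPG "of 7.8 mmol/L (140 mg/dL) to 11.0 mmol/L (199 mg/dL" after the glucose load, and HbA1c of 5.7–6.4%. One is enough: "Participants who satisfy one of the above criteria will be diagnosed with prediabetes". Inclusion criteria adopts this rule and adds age 18–50 and a signed consent form.
- **Exclusion.** The one item in Exclusion criteria that names diabetes is "History of diabetes (except gestational diabetes". No item refers to a glucose or HbA1c value found at screening.
- **Baseline testing.** Primary outcomes are FPG, 2-hPG and HbA1c, and "All the primary outcomes will be tested on visit 1 (within 1 week before the study" is the first of three test points.
- **Diabetes endpoint.** Endpoint events gives "Occurrence of type-2 diabetes (according to the 2016 ADA diagnostic criteria for prediabetes [40, 41". Under Additional indicators, incidence is the number of diabetes cases divided by the total in each group, and it "will be calculated only on visit 26 (after 48 weeks". Neither numerator nor denominator removes people above range at visit 1. Arms are compared by chi-square.
- **Concomitant drugs.** Bias control says that "drugs that have antidiabetic therapeutic effects will be prohibited".

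**The concern.** An incidence comparison needs a group free of the event at the start. Here the entry rule looks for one index inside a range and is silent on the other two. A person with FPG 6.2 mmol/L and 2-hPG 12 mmol/L, first detected at screening, qualifies on FPG and has no history of diabetes.

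If that person is still above threshold at visit 26, the formula counts a case that was present before randomisation. Such cases raise incidence in both arms and tend to pull the ratio between arms towards 1. With 40 per arm and few expected events, a chance imbalance of two or three of them can also shift the comparison noticeably. Their glucose values enter the *t* tests on the primary outcomes, and they sit in the denominator of the reversion rate.

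These participants would also be in a trial that prohibits antidiabetic drugs, under a protocol written for prediabetes. The documents do not reconcile those two provisions.

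**Working it through.** No figure in the plan can be reproduced for this point. The sample size of 40 per group is attributed to limited funds and a lack of preliminary studies, without an effect size. The check is therefore a test of the rule, followed by an illustration.

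**1. The rule applied literally.** Eligible if FPG is 5.6–6.9, or 2-hPG is 7.8–11.0, or HbA1c is 5.7–6.4.

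| FPG (mmol/L) | 2-hPG (mmol/L) | HbA1c (%) | Above range on | Eligible? |
|---|---|---|---|---|
| 6.5 | 12.0 | 6.0 | 2-hPG | yes |
| 5.2 | 12.0 | 6.1 | 2-hPG | yes |
| 7.4 | 9.0 | 6.2 | FPG | yes |
| 6.0 | 9.0 | 6.8 | HbA1c | yes |

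**2. Expected true incidence without treatment effect, c.** The Background cites 5–11% a year and 24.3% in 2 years. The latter is 1 − √(1 − 0.243) = 13.0% a year. With annual rate a, c = 1 − (1 − a)^(weeks/52). Both horizons are shown because visit 26 is described as after 48 weeks, while the study period is 24 + 48 = 72 weeks.

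| Annual rate | c, 48 weeks (cases per 40) | c, 72 weeks (cases per 40) |
|---|---|---|
| 5% | 4.6% (1.8) | 6.9% (2.7) |
| 11% | 10.2% (4.1) | 14.9% (6.0) |
| 13.0% | 12.1% (4.8) | 17.5% (7.0) |

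**3. Observed risk ratio.** Let v be the share above range at entry. Assume v = 5% or 10% (2 or 4 per arm of 40), a true risk ratio of 0.50 in the rest, and every above-range entrant still above threshold at visit 26 in both arms. Then

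observed RR = [v + (1 − v)c/2] / [v + (1 − v)c].

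- Least dilution, 72 weeks (v = 5%, c = 17.5%): 0.1333 / 0.2165 = 0.62.
- Most dilution, 72 weeks (v = 10%, c = 6.9%): 0.1309 / 0.1617 = 0.81.
- The same extremes at 48 weeks: 0.1073 / 0.1645 = 0.65 (v = 5%, c = 12.1%) and 0.1208 / 0.1416 = 0.85 (v = 10%, c = 4.6%).

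**4. Sensitivity to persistence.** If only half stay above threshold, equally in both arms (also an assumption), v is replaced by v/2 in the two leading terms. The 72-week extremes become 0.1083 / 0.1915 = 0.57 and 0.0809 / 0.1117 = 0.72.

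**5. Chance imbalance.** With 4 such people among 80 (5%), the probability that the arms differ by at least two is 0.62. With 8 (10%) it is 0.71. Both are hypergeometric, for 40 against 40.

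**6. Power of the incidence comparison.** For an assumed 15% against 7.5% with 40 per arm, approximate power is 18% with no above-range entrants, and 14% or 11% with v = 5% or 10%, all persisting.

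**The case against.** **The intent is probably otherwise.** The ranges have upper limits, they stand under a diagnosis of prediabetes, and the Background treats diabetes as a later state. *Occurrence* suggests new onset, and endocrine disease is an exclusion. This is a fair account of intent, but none of these sets a ceiling at visit 1. The endocrine item does not name diabetes or a glucose value, and diabetes has its own item limited to history. The incidence formula does not enforce new onset.

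**Screening may catch these people.** Visit 1 falls in the screening week, and the visit contents are in a figure and additional files not shown. It therefore cannot be said that the visit-1 results go unused. It can be said that the stated eligibility criteria do not use them as a ceiling.

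**Incidence is not the primary outcome.** It is an endpoint event, listed under Additional indicators, in what the Sample size section calls a pilot design. The primary outcomes are continuous. Power is also low without any above-range entrant. This stands and limits the severity.

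**The size is assumed.** The 5–10% share has no source in the documents, and full persistence is a worst case for dilution: both arms receive lifestyle programmes, and the treatment is meant to lower glucose. This stands too.

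**Stronger readings to avoid.** A reader might infer that the investigators plan to enrol people with diabetes, that the incidence result will be biased in favour of treatment, or that the trial cannot proceed unless this is changed. The text shows only that such enrolment is permitted. Randomisation makes the effect non-differential in expectation, so the main results are dilution and noise.

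**Conclusion.** The gap in the text is real: the entry rule, the history-only exclusion and the incidence formula together allow a person above range on one index at visit 1 to be enrolled and counted as a case at visit 26. The expected consequence is inflated incidence in both arms and a contrast that tends to be diluted. Chance imbalance and above-range values in the primary comparisons add noise; the effect on the primary means was not quantified.

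How large this would be is unknown. The range of 0.62–0.81 for a true 0.50 is an illustration that rests on an assumed 5–10% share, full persistence in both arms and a 72-week horizon. Half persistence gives 0.57–0.72; a 48-week horizon with full persistence gives 0.65–0.85.

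This should be fixed, but it does not undermine the trial's primary comparison.

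**What to change.** Add one item to Exclusion criteria: any visit-1 FPG, 2-hPG or HbA1c above the upper limit already stated in Diagnostic criteria (6.9 mmol/L, 11.0 mmol/L, 6.4%). State that it is checked on the visit-1 results before randomisation.

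Separately, the sponsor should reconcile the entry rule with the prohibition of antidiabetic drugs in Bias control.

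The cost is one eligibility line and a few more screen failures. All three tests are already scheduled at visit 1, and the 40 per group is unchanged. Trial status says that the trial had not started at submission. The change belongs before enrolment, because removing such people later would be a post-randomisation exclusion.

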#### Inclusion criteria

Fulfill the prediabetes diagnostic criteriaBe aged 18–50 years oldCompleted and submitted an ICF

#### Exclusion criteria

History of diabetes (except gestational diabetes)Cardiovascular and cerebrovascular events (cerebrovascular accident in past 6 months, history of myocardial infarction or heart failure; severe organic heart disease; aneurysm of a main artery or dissecting aneurysm; specific angina; type II degree atrioventricular block; sick sinus syndrome)Impairment of hepatic or renal function: abnormal alanine aminotransferase (ALT), aspartate aminotransferase (AST), blood urea nitrogen (BUN) or creatinine (Cr)Endocrine disease, such as hyperthyroidism, autoallergic disease, cancer or other serious or potentially fatal illnessPregnancy, preparation for pregnancy or active lactation in womenPatients with mental illness or those who are uncooperativeParticipation in other clinical trial within the last 2 weeksRefusal to provide consent for the study

#### Rejection criteria

Did not receive acupuncture treatment or take herbal medicines according to the protocolIncomplete data

#### Suspension criteria

Poor complianceSerious adverse events (SAEs) or complications or unique physiological changesReluctance to continue the trialWithdrawal for various reasons such as failure to follow-up or deathIncomplete information that would influence the trialLarge error in protocol or significant deviation in implementationDecision to terminate the trial by national law, the Ministry of Science and Technology or other authority

#### Dropout criteria

Experience SAEs that should stop intervention immediatelyRefuse to receive any kind of intervention or ask for suspensionFailure to follow-up before all data of primary outcomes have been taken

Researchers should try their best to contact participants by using all kinds of possible methods to ascertain the reasons for dropping out and the last time that they had taken the decoction, and ask them to finish the examinations as far as they possibly can. If the participants experience any adverse events (AEs) during the study, researchers should provide appropriate treatment for them. The expected dropout rate should be less than 15%. The dropout cases will be included in the statistical analysis.

### Follow-up

#### Data collection points

Figure 1 shows the table of data collection points based on the Standard Protocol Items: Recommendations for Interventional Trials (SPIRIT) figure.Screening period: 1 week before the interventionIntervention period: 24 weeks; once a week for 24 weeksFollow-up period: 48 weeks after the intervention

**Fig. 1 Fig1:**
[figure not shown]
Content for the schedule of enrolment, interventions, and assessments

#### Contents

See Additional file 1. Data should be captured according to Additional file 2.

### Outcome measures

#### Endpoint events

Occurrence of type-2 diabetes (according to the 2016 ADA diagnostic criteria for prediabetes [40, 41])Blood glucose change to normal (FPG <5.6 mmol/L, OGTT 2-hPG <7.8 mmol/L, and HbA_1c_ <5.7%)

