#### Statistical analysis method

Student’s *t* test will be used for group comparison (treatment group versus control group) on primary outcomes and secondary outcomes. the chi-square test will be used for comparing the endpoint events (occurrence of type-2 diabetes and blood glucose change to normal).

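### The endpoint event of type-2 diabetes is defined by the prediabetes criteria, so at visit 26 it would mainly count failure to revert

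*Protocol article*

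**What the plan says.** The Endpoint events section of the protocol article lists two events. The first is "Occurrence of type-2 diabetes (according to the 2016 ADA diagnostic criteria for prediabetes", with references 40 and 41. The second, return to normal glucose, has explicit cut-offs: FPG below 5.6 mmol/L, 2-hPG below 7.8 mmol/L and HbA1c below 5.7%, all three required.

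The prediabetes criteria are set out under Diagnostic criteria, whose heading cites the same year and references ("according to the ADA criteria for a diagnosis of prediabetes in 2016 [40, 41"). They are three ranges, each with an upper bound: "FPG of 5.6 mmol/L (100 mg/dL) to 6.9 mmol/L (125 mg/dL"), a 2-hPG of "7.8 mmol/L (140 mg/dL) to 11.0 mmol/L (199 mg/dL"), and an HbA1c of 5.7 to 6.4%. Any one is enough: "Participants who satisfy one of the above criteria will be diagnosed with prediabetes". Inclusion criteria makes meeting them a condition of entry. Diabetes is excluded by history only: "History of diabetes (except gestational diabetes").

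Additional indicators gives the incidence as diabetes cases over all cases in the group, calculated at visit 26 only, without saying what a diabetes case is. Statistical analysis method assigns the chi-square test to "comparing the endpoint events (occurrence of type-2 diabetes and blood glucose change to normal").

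**The concern.** The event that should mark leaving prediabetes for diabetes is defined by the criteria for being in prediabetes. Because the ranges have an upper bound, the definition is not just too broad. It takes in people who have not progressed and can leave out people who plainly have.

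The abstract names the incidence of diabetes as an endpoint index, it has its own formula and its own test, and the Discussion hopes to see it improved. If the printed rule is followed, the reported figure answers a different question. If it is not followed, someone must choose thresholds and a combination rule that the article does not state, possibly after data exist.

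**Working it through.** The article states no alpha, power or effect size, and 40 per group is a pilot choice set by funding, so there is no calculated figure to reproduce. The check applies the printed rule to example participants and then puts the result on a scale.

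**Step 1. The rules.**
- Printed diabetes event: FPG 5.6–6.9 mmol/L, or 2-hPG 7.8–11.0 mmol/L, or HbA1c 5.7–6.4%.
- Normal: FPG below 5.6 and 2-hPG below 7.8 and HbA1c below 5.7%.
- Above a limit: FPG above 6.9, or 2-hPG above 11.0, or HbA1c above 6.4%.

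**Step 2. Illustrative profiles at visit 26.**

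| FPG / 2-hPG / HbA1c | Printed diabetes event | Normal | Above a limit |
|---|---|---|---|
| 6.2 / 7.0 / 5.5% | yes | no | no |
| 5.2 / 9.0 / 5.5% | yes | no | no |
| 5.2 / 7.0 / 6.0% | yes | no | no |
| 8.0 / 13.0 / 6.3% | yes, through HbA1c alone | no | yes |
| 8.0 / 13.0 / 7.2% | no | no | yes |
| 8.0 / 13.0 / 5.5% | no | no | yes |
| 5.0 / 6.5 / 5.3% | no | yes | no |

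The first three rows are people whose prediabetes merely persists, and all count as diabetes. A progressor is missed when no index lies inside a range. The plain case is all three above. The sixth row, with one index below its range and the others above, is a further case.

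**Step 3. What the printed incidence measures.** Let r be the proportion who revert and m the proportion who are not normal but have no index inside a range. With complete data, printed incidence = 1 − r − m. The documents give no reversion rate, so r is an assumption:
- r = 10%: at most 90%, 36 of 40
- r = 30%: at most 70%, 28 of 40
- r = 50%: at most 50%, 20 of 40

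If m is zero in both arms, the incidence table is the reversion table with its columns swapped, and the two chi-square tests give the same statistic.

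**Step 4. Scale of true progression.** The Background gives 5–11% a year in prediabetes, and 24.3% per 2 years in IGT. Assuming a constant rate, with t in years:

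72 weeks (24 of intervention plus 48 of follow-up), t = 72/52 = 1.385:
- 1 − 0.95^1.385 = 6.9%; × 40 = 2.7
- 1 − 0.89^1.385 = 14.9%; × 40 = 6.0
- 1 − 0.757^(1.385/2) = 17.5%; × 40 = 7.0

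The article labels visit 26 only as after 48 weeks. If that meant 48 weeks from entry, t = 48/52 = 0.923:
- 1 − 0.95^0.923 = 4.6%; × 40 = 1.8
- 1 − 0.89^0.923 = 10.2%; × 40 = 4.1
- 1 − 0.757^(0.923/2) = 12.1%; × 40 = 4.8

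**Step 5. Whether new thresholds alone are enough.** Someone with FPG 6.2 mmol/L and HbA1c 6.6% meets the FPG range, so qualifies for entry, and has no recorded history of diabetes to exclude them. With HbA1c unchanged, they would be an incident case at visit 26 under an any-index-above-limit rule, although nothing happened during the trial.

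**The case against.** The best defence is that this is one wrong word. Occurrence implies a new event, the rest of the article keeps diabetes and prediabetes apart, and the stated hope of stopping one turning into the other makes no sense under the literal rule. The two references and the additional files are not shown and may contain the diabetes criteria. The first part stands: it is probably a slip. It does not remove the problem, because the article prints a definition and that definition is wrong. Nothing else in it supplies thresholds, a combination rule or a confirmation rule.

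Three stronger readings are tempting, and the text does not support them.
- A reader might infer that all 40 per arm are counted as diabetic at entry. They do meet the printed criteria then, but Additional indicators restricts the incidence to visit 26, so that count is never made.
- A reader might infer that progression is scored as success. A missed progressor drops out of the diabetes count but is not counted as reverted, because normalisation needs all three values below their cut-offs. Progressors with an index still in range are counted.
- A reader might infer that the trial's main comparison is compromised. The primary outcomes are the continuous FPG, 2-hPG and HbA1c levels, compared by t test, and do not use this definition. The normalisation endpoint does not use it either.

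It is also fair to say that incidence is listed under Additional indicators in a trial called a pilot, and that a correct definition would yield few events. That limits the weight of the result but does not justify a wrong definition of a named and tested endpoint.

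**Conclusion.** The concern holds in a limited form. As printed, the diabetes endpoint at visit 26 counts persisting prediabetes as diabetes and omits anyone with no index left inside a prediabetes range, most clearly a participant above all three. The resulting incidence is close to the complement of the reversion rate. This follows from the text and needs no outside figure.

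The size is only indicative. The contrast is up to 70% (28 of 40) at an assumed 30% reversion, against about 7% to 18% (3 to 7 of 40) from the article's background rates over 72 weeks, or about 5% to 12% (2 to 5 of 40) if the horizon is 48 weeks. The upper rate in each case comes from people with IGT, whereas this trial also admits people on FPG or HbA1c alone. The damage is confined to the diabetes incidence and its chi-square test.

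**What to change.** 1. Under Endpoint events, replace the prediabetes criteria with the diabetes criteria and print the thresholds. To agree with the article's own upper limits, these would be any of FPG above 6.9 mmol/L, 2-hPG above 11.0 mmol/L or HbA1c above 6.4%.
2. State that the event counts as new only if no index was above its limit at visit 1, and whether a participant who was already above a limit stays in the denominator.
3. Say whether one reading on one index is enough.
4. Use this single definition in the incidence formula under Additional indicators and in the chi-square test under Statistical analysis method.

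The cost is a few sentences. All three indices are already measured at visits 1, 25 and 26, so no new data are needed unless the sponsor decides to require a confirmatory reading. The trial had not started when the article was submitted. If it has started since, the change should be made and dated before outcome data are examined by group.
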